# Sheffield Adaptive Patterned Electrical Stimulation (SHAPES) Therapy for Post Stroke Arm spasticity: study protocol for a 3-arm, a partially blinded, randomised controlled trial

**DOI:** 10.1186/s12883-024-03635-x

**Published:** 2024-11-09

**Keywords:** Stroke, Spasticity, Electrical stimulation, TENS, SHAPES, RCT

## Abstract

**Introduction:**

Post stroke elbow spasticity (PSES) affects over a third of individuals following stroke and negatively impacts on functional recovery, comfort and quality of life. Drug therapies have limited efficacy and unwanted side effects, botulinum toxin, although effective, is costly, and conventional electrical stimulation therapies are limited long term by habituation. We aim to investigate the efficacy of Sheffield Adaptive Patterned Electrical Stimulation (SHAPES), that delivers temporally and spatially varying pattern of electrical stimulation, against transcutaneous electrical stimulation (TENS) and standard care at reducing PSES.

**Methods and design:**

Overall, 297 people with PSES will be randomised (1:1:1) to one of 3 arms: Standard care (no electrical stimulation), TENS (conventional patterned electrical stimulation) or SHAPES (adaptive patterned electrical stimulation). Both SHAPES and TENS are delivered using a specially designed electrical stimulation sleeve used for 60 min each day for 6-weeks. Outcome measures are completed at baseline, end of treatment (EOT 6 weeks) and then 6-weeks, 12-weeks and 24-weeks after the end of treatment. Efficacy will be determined based on the proportion of participants experiencing meaningful improvement (18%) in the 7-day Numerical Rating Scale (NRS-S) for PSES, compared between both intervention arms and standard care, and between the two intervention groups. Measures of arm motor function (Action Research Arm Test, MRC scale), and quality of life (SQoL-6D, EQ-5D) will also be measured along with a parallel health economic evaluation.

**Discussion:**

The results of the SHAPES trial will inform management of elbow spasticity after stroke. The SHAPES intervention is a low cost, self-administered intervention for the management of spasticity that can be used repeatedly, and if found to be more effective than TENS or control has the potential to be widely implemented in the UK NHS healthcare setting. Furthermore, despite the wide use of TENS in the management of spasticity, this study will provide critically required evidence regarding its efficacy. The trial has been registered with the ISRCTN registry (ISRCTN26060261).

**Supplementary Information:**

The online version contains supplementary material available at 10.1186/s12883-024-03635-x.

## Introduction

There are over 1 million stroke survivors in the UK, with over 100,000 new cases each year [1] making it one of the leading causes of adult death and disability. An ageing and more multi-morbid population mean the number of stroke survivors aged 45 years or over is expected to rise by 123% over the next 20 years [2]. Long term upper limb impairment affects 40–50% of people in the chronic phase of stroke [3] and can manifest as weakness, apraxia, sensory disturbance, or spasticity.

Spasticity is a velocity dependent increased resistance to passive stretch and hyperactivity of stretch reflexes [4] that can result in pain, spasms, reduced range of movements, and ultimately contractures. Arm spasticity affects over a third of people with arm weakness a year after stroke [5] and impacts greatly on return to function and quality of life [6]. Treatment strategies for spasticity exist, however they each have limitations that mean spasticity is still a difficult complication to manage. Management of triggers known to aggravate spasticity and traditional stretching therapies remain the cornerstone of spasticity management but can be labour intensive if delivered by trained therapists or therapy assistants. Oral anti-spasticity medications, such as Baclofen in high doses can be effective, however, they have considerable side-effects, including sedation, weakness, confusion, and depression. Medication adherence with oral antispasticity drugs is poor, typically between 15% and 50% [7]. Botulinum toxin injections can relax spastic muscle for up to 12 weeks, without side-effects of global weakness or sedation, however they can take several weeks to become effective, and are resource heavy in terms of the need for repeated injections delivered in specialist clinics. This can have the effect of at least doubling direct care costs of managing spasticity [8]. Improved therapies for spasticity are much needed.

One such alternative therapy includes neuromuscular electrical stimulation (NMES) techniques, such as transcutaneous electrical stimulation (TENS). Stimulation of peripheral sensory nerves is thought to induce neuroplastic change in spinal cord pathways, leading to inhibition of spinal motor neurones [9]. TENS is an attractive option, given its low cost and ease of administration. Meta-analyses of randomised controlled trials (RCTs) evaluating the effects of TENS for spasticity demonstrate moderate improvements in spasticity severity and limb range of motion compared to control [10] but these improvements are often short lived. The recent NICE guidelines on stroke rehabilitation in adults 2023 recommends research on cost effectiveness of NMES therapies like TENS [11].

TENS often use single channel, single strength, fixed duration modes of stimulation to which the nervous system may get habituated. Habituation is the reduction in neuromuscular response to a repeated stimulus and is associated with a decrease in transmitter release from synaptic afferent nerve terminals, due to inactivation of calcium channels in the presynaptic membrane [12]. One way to try and mitigate the effects of habituation is to alter the pattern of electrical stimulation delivered. Indeed, alternating the frequency of electrical stimulation delivered by TENS had the effect of reducing habituation and improving duration of effect when delivered for pain management compared to non-modulated TENS [13]. With this in mind, the department of Clinical Engineering at Sheffield Teaching Hospitals, in collaboration with neurorehabilitation clinicians, underwent a series of co-development stages to co-design the Sheffield Adaptive Patterned Electrical Stimulation (SHAPES) therapy with people with lived experience of stroke [14]. In an initial proof of concept study, 10 patients with elbow flexor spasticity, Modified Ashworth Score (MAS) ≥ 2, underwent both TENS or SHAPES stimulation for 60 min just below the threshold for motor activation, in a randomised order, a week apart. Immediately following stimulation, spasticity (MAS and visual analogue scale 0-100) improved following both types of stimulation but persisted for up to an hour following SHAPES stimulation only [15]. Subsequently a single blind, crossover, randomised controlled feasibility trial recruited and randomised 16 patients with post stroke elbow spasticity (PSES) to receive either TENS or SHAPES, delivered once daily for 60 min, for 4 weeks before switching to the other treatment modality after a 2-week washout period. The intervention, delivered by patients themselves or care givers was safe, acceptable, and feasible [16].

The Sheffield Adaptive Patterned Electrical Stimulation (SHAPES) study aims to assess the efficacy of SHAPES and TENS electrical stimulation therapy for PSES. It will also provide a health economic analysis to guide implementation in the UK healthcare setting. The protocol is presented according to the Standard Protocol Items: Recommendation for International Trials checklist [17].

### Study objectives

#### Primary objectives

To determine whether SHAPES and/or TENS interventions lead to a greater proportion of participants with PSES experiencing meaningful improvements in spasticity (NRS-S change > 18% compared to usual care) after 6 weeks of treatment.To determine whether the SHAPES intervention leads to a greater proportion of participants with PSES experiencing meaningful improvements in spasticity compared to TENS after 6 weeks of treatment.

#### Secondary objectives

To determine whether any differences in efficacy relating to spasticity reduction described above between groups persists at 6 weeks, 12 and 24 weeks after end of treatment.To investigate between-group differences in changes to other measures including Modified Ashworth Scale (MAS), arm motor function (Action Research Arm Test, ARAT) and strength (Medical Research Council, MRC strength scale), spasticity impact (Leeds Arm Spasticity Impact Scale, LASIS) and European Quality of Life Scale 5D-5 L (EQ-5D) and spasticity specific quality of life scale (SQoL-6D).To develop a health economic model to inform a cost-effectiveness analysis for the UK healthcare system.

## Methods and design

### Design

A partially blind, multi-site, 3-arm randomised control trial, evaluating the change in elbow spasticity after six weeks of intervention measured by NRS-S and with the key outcome of interest being the proportion in each group that achieve an improvement of 18% in 7-day average NRS-S between the two time points. The investigation compares the efficacy of the SHAPES stimulation to TENS stimulation and both compared to usual care at different time points.

### Study setting and timeline

The trial is being conducted in South Yorkshire, UK, that includes hospitals delivering care for approximately 1 million people in Sheffield, Rotherham, and Doncaster. Study assessments and procedures are taking place at the NHS facilities of Sheffield Teaching Hospitals NHS Foundation Trust, UK. The study opened for recruitment in June 2023 and will recruit to December 2024.

### Participants

We calculated the sample size using data from our previous study [15]. The sample size calculation for a two group t-test for equal means showed that to conduct a three arm randomized control trial of SHAPES, TENS and ‘usual care’ control, we would need 66 subjects per group (total 198 participants) to have 90% power to demonstrate a MCID reduction of 18% in NRS at the 1% significance level to allow for multiple testing. In our feasibility study 67% of participants showed good adherence with the intervention and 73% with recording of NRS. We will recruit a total of 297 patients with PSES to the study who are being randomised to one of the 3 arms. We aim to achieve a minimum of sixty-six (66) participants to adhere to and complete the protocol in each group with good adherence to the intervention schedule and a minimum of 4 of 7 daily NRS-S recording.

Patients will be eligible to participate according to the inclusion and exclusion criteria listed in Table 1. Patients must be between 2 and 26 weeks from the onset of stroke and have any degree of arm spasticity (MAS ≥ 1) with at least mild weakness of the elbow flexors (MRC ≤ 4). Those with implantable electrical stimulation devices, participating in other interventional upper limb studies, or with pre-existing musculoskeletal of neurological disorders affecting elbow movement or spasticity are excluded. Aphasia and cognitive impairment are not exclusion criteria as long as patients can understand the intervention and complete study outcome measures.

Potentially eligible participants are identified by treating clinicians working in the stroke and rehabilitation services at Sheffield, Rotherham and Doncaster. Treating clinicians provide potential participants with the study information and obtain their consent to contact. Central researchers at Sheffield will call those consenting to be contacted via telephone to arrange a screening visit if they are willing to participate.

### Study procedures

At the screening visit, participant written informed consent is obtained by study researchers, eligibility confirmed by a medical doctor of the study team, demographic data recorded, and a baseline assessment of healthcare utilisation recorded. The participant is trained on recording daily NRS-S for 7 days (baseline assessment), recorded either using a dedicated smartphone ‘App’ or as a paper diary to suit their preference. The average of which (minimum 4 of 7 days scores) forms the baseline 7-day NRS-S score, completed prior to attending Visit 2. The participant is then be randomised (1:1:1) to either:

SHAPESTENSUsual care

**Table 1 Tab1:** Study inclusion and exclusion criteria

**Inclusion Criteria**
1. Age 18 to 100 years
2. 2-26 weeks after stroke
3. Weakness of elbow extension of MRC grade 4 or below
4. Spasticity of elbow, of grade-1 or more on the Modified Ashworth Scale (MAS) of elbow flexion
**Exclusion Criteria**
1. Dermatological, rheumatologic or orthopaedic illnesses of the affected arm interfering with elbow movement
2. Pre-existing severe systemic disorders like cardiovascular disease, active cancer or renal disease, end stage pulmonary or cardiovascular disease, psychiatric illness including severe alcohol or drug abuse and depression
3. Expected inability to perform the baseline assessments such as in those with severe aphasia or dysphasia
4. Severe tactile hypersensitivity
5. Participation in other, spasticity related studies
6. Within 12 weeks of receiving elbow flexor Botulinum toxin injections
7. Uncontrolled epilepsy
8. Any form of implanted electrical / electronic device
9. Pregnancy
10. Inability to provide informed consent
11. Pre-existing upper limb spasticity
12. Previous acute contact dermatitis and/or known allergy to acrylates.
13. Within 2 weeks of receiving, or planned future use of, other forms of electrical stimulation to the elbow flexors or extensors

Randomisation is facilitated by blinded researchers using Castor EDC clinical trials management software, which employs validated variable block randomisation model. Its algorithm is constructed in such a way that randomised inclusions are divided across groups in variable block sizes, which is intended to ensure true randomness during the allocation.

At the second study visit, other baseline outcome measures are completed. Participants in the SHAPES or TENS arms receive a specially designed upper limb electrical stimulation system (ShefStim APS) and are trained on how to apply and use the device each day during the intervention period. All devices are configured to the allocated TENS or SHAPES arms of the study using a QR code to maintain blinding. Participants then deliver the intervention at home independently or with the help of a care giver for 6 weeks. After 2–3 weeks all participants are contacted to check that they are managing the NRS-S diary, with those in the device arms also receive a safety / device review with the study team. At the end of the 6-week intervention period they return for end of treatment outcome measures that also include an assessment of healthcare utilisation. These assessments are repeated at 6 weeks, 12 weeks and 24 weeks after the end of intervention period. All participants are invited to undergo experiential interviews, providing qualitative data on intervention use. While participants and clinicians facilitating the treatment checks will not be blinded to the control group, outcome measures will be undertaken by researchers blinded to treatment allocation, while all participants and researchers undertaking outcome measure assessments will be blinded to type of electrical stimulation.

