#### SHAPES

Each horizontal row of 8 electrodes on the array is sequentially activated for 0.3s at a pulse repetition frequency of 50 Hz and with a pulse width of 250µs. After all 8 rows of electrodes have operated the stimulation pauses for 2.5s before the sequence is repeated.

The participants in the usual care arm do not receive any device. The systems are programmed following randomisation allocation, using a QR code that is scanned onto a stimulator remote control (repurposed Alcatel 1c smartphone) and delivered via Bluetooth LE to the stimulator box. The participant’s mid-bicep circumference is be measured and the oversized sleeve cut to size to ensure that a personalised sleeve fit is achieved. When applied, the biocompatible hydrogel layer should contact the skin overlying the extensor aspect of the affected upper limb, over the triceps area. During the setup of the ShefStim APS (for those in the SHAPES or TENS arms of the study) the stimulation intensity (current) is gradually increased until the underlying muscle begins to twitch (motor threshold, MT). If the participant experiences any discomfort from the stimulation, the intensity is limited to the highest that is comfortable for them. The stimulation level is then set to 90% of the MT or, if the MT was not reached, 90% of the maximum comfortable level. This intensity is recorded at baseline and becomes the default level for home use. Participants are trained on how to apply the sleeve and, if necessary, adjust the stimulation intensities (within clinically set levels) for comfort.

During the intervention participants can receive all usual cares for spasticity management provided by the NHS (e.g. botulinum toxin, oral agents, stretching exercises etc.). This will be recorded and compared between the 3 groups and adjusted for in the statistical analysis.

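### Exclusion 1 tests skin disease of the arm by its effect on elbow movement, so most active skin disease or a wound at the electrode site does not bar entry; minor, and cheap to fix

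*Protocol article*

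**What the plan says.** Three of the 13 exclusions in Table 1 of the protocol article bear on the skin or its sensitivity:

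- Exclusion 1: "Dermatological, rheumatologic or orthopaedic illnesses of the affected arm interfering with elbow movement".
- Exclusion 4: "Severe tactile hypersensitivity".
- Exclusion 12: "Previous acute contact dermatitis and/or known allergy to acrylates".

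The narrative eligibility text under Participants adds no skin criterion.

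Under Interventions and control, "the biocompatible hydrogel layer should contact the skin overlying the extensor aspect of the affected upper limb, over the triceps area". The device is used for 60 minutes a day for 6 weeks. On the order of events, the same section says that "The systems are programmed following randomisation allocation" and that "The participants in the usual care arm do not receive any device". Study procedures places the hand-over of the device at the second visit: "Participants in the SHAPES or TENS arms receive a specially designed upper limb electrical stimulation system".

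The section on pre-defined withdrawal criteria lists an injury or skin condition at the back of the upper arm, arising during the trial, as a reason to stop the intervention. It attaches no condition about elbow movement. Such participants remain under outcome assessment, and the analysis is by intention to treat.

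**The concern.** On its natural reading, the elbow-movement qualifier in exclusion 1 governs all three kinds of illness that it names. That suits joint and bone disease. It does not suit skin disease in a trial of a surface electrode, where the question is whether the skin can take the hydrogel. Infected skin or active psoriasis over the triceps can leave the elbow moving freely.

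The main stake is trial conduct. A patient who cannot wear the electrodes is identified after randomisation instead of before it. The consequence is one-sided: a usual-care patient with the same skin has no device to forgo. A small skin-safety risk comes with it.

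**Working it through.** The document gives no figure to reproduce. The check is mainly a reading of the criteria, followed by an illustration of size.

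**Step 1: do the entry criteria cover the condition?** Take a patient with free elbow movement and one of these over the triceps:

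| Condition | Exclusion 1 | Exclusion 4 | Exclusion 12 |
|---|---|---|---|
| Wound or unhealed injury | no | no | no |
| Skin infection | no | no | no |
| Active eczema (not contact dermatitis) or psoriasis | no | no | no |
| History of acute contact dermatitis, or acrylate allergy | no | no | yes |

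The other ten exclusions and the four inclusion criteria do not address skin. The gap is real except in the last row.

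**Step 2: how do the stopping reasons compare with the entry criteria?**

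| Reason to stop the device | Matching exclusion |
|---|---|
| New implanted device | 8 |
| New stroke | none needed; by nature an on-study event |
| Allergy to electrodes or gel | 12 (acrylates) |
| Injury or skin condition at the back of the upper arm | none without the elbow-movement test, apart from the contact dermatitis in 12 |
| Significant medical illness | broadly 2 |
| Pregnancy | 9 |

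The skin and injury item is the one stopping reason that can already be present at baseline without an adequate entry counterpart.

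**Step 3: when is the problem found?** The sequence in Study procedures is: screening visit, 7-day baseline diary, randomisation, then device fitting at the second visit in the two device arms. A lesion might be noticed in any arm at that visit, but only in the device arms does it change what the patient receives.

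**Step 4: illustrative size.**

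- From the document: 297 patients allocated 1:1:1, so 297/3 = 99 per arm.
- Assumed, with no source in the document: 1% to 3% of patients affected. That is 0.01 × 297 = 3.0 to 0.03 × 297 = 8.9, or about 3 to 9 patients: 1 to 3 per arm and 2 to 6 in the two device arms together.
- Also assumed: affected patients never use the device and respond as usual care does.

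Let k be the number of non-users in a device arm, p_D the response proportion among users and p_U the proportion under usual care. The intention-to-treat difference is

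[(99 − k)·p_D + k·p_U]/99 − p_U = (1 − k/99)·(p_D − p_U).

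- k = 1: shrinkage 1/99 = 1.0%; an assumed 20-point difference becomes 20 × 98/99 = 19.8.
- k = 3: shrinkage 3/99 = 3.0%; the same difference becomes 20 × 96/99 = 19.4.

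With equal k in both device arms, p_U cancels and the SHAPES versus TENS difference shrinks by the same factor.

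For any given prevalence these are upper bounds, because a patient whose skin heals can start late and gain part of the benefit.

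**Step 5: exposure if fitting misses the lesion.** There are 6 × 7 = 42 daily sessions. The safety and device review at 2 to 3 weeks would come after 2 × 7 = 14 to 3 × 7 = 21 of them.

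**The case against.** **The article condenses a fuller protocol.** Inspection of the electrode site, device contraindications and a screening checklist may stand in documents not shown. Their absence here is not a fault, and this point does not rest on it. It rests on a criterion that is printed and that judges skin disease by the wrong property.

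**The qualifier may attach only to orthopaedic illness.** That is the less natural reading. It would bar any rash or arthritis anywhere on the arm and make the contact dermatitis in exclusion 12 largely redundant for that arm. If it is what was meant, the wording still needs correcting.

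**Other safeguards would catch most cases.** This largely stands. A study doctor confirms eligibility, fitting is supervised, "If the participant experiences any discomfort from the stimulation, the intensity is limited to the highest that is comfortable for them", and device users have the early safety review. Staff who know the stopping rule are unlikely to start stimulation on damaged skin. These safeguards limit the safety risk. However, the doctor confirms the written criteria, which do not bar such a patient, and fitting comes after allocation.

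**The effect is negligible and already allowed for.** This also largely stands. The plan randomises 99 per arm to obtain 66 adherent, a margin of 33, and foresees sensitivity analyses for non-compliance. One to three patients per arm fit well within that margin.

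**Stronger readings.** A reader might infer that the withdrawal section contradicts Table 1. It does not: it concerns conditions that arise after entry, so the two sections differ in standard without conflicting. A reader might also infer a serious safety hazard, a power shortfall or a bias in favour of the device. The document supports none of these. The safeguards above limit the hazard, the recruitment margin absorbs the numbers, and under the assumptions of Step 4 the distortion is towards no effect.

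**Conclusion.** The concern holds as a minor wording fault. Apart from people with previous acute contact dermatitis or acrylate allergy, a patient with a wound, infection or other active skin disease over the triceps and free elbow movement is eligible as written, although the protocol would stop the device if the same condition appeared later.

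Any non-use or late start falls only on the SHAPES and TENS arms and remains in their intention-to-treat comparison with usual care. The effect on the primary result is small and conservative. The document does not allow its size to be derived: the 1.0% to 3.0% shrinkage depends wholly on the assumed 1% to 3% prevalence and on complete, permanent non-use, so it is an illustrative upper bound.

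**What to change.** Add one exclusion to Table 1: *Broken, infected or actively inflamed skin, or an unhealed injury, over the extensor aspect of the affected upper arm (electrode site) that would preclude electrode use.* Leave exclusions 1, 4 and 12 and the withdrawal criteria as they are. Trivial lesions that allow electrode use stay eligible.

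Check the criterion in all patients at the screening visit and reconfirm it immediately before randomisation. The 7-day diary lies between the two, so a lesion can appear or heal in that time. Allow re-screening after healing while the patient is still within 26 weeks of stroke.

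The cost is a one-line amendment, one more checklist item and two brief looks at the skin over the triceps. A few patients will be delayed, or lost if they pass 26 weeks; the document does not give their number. Recruitment was planned to end in December 2024, so the change helps only patients not yet enrolled.

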### Safety reporting

While prior studies have not demonstrated any safety concerns associated with TENS of SHAPES in the management of spasticity [15, 16] safety outcomes will also be reported. The following definitions will be applied in the reporting of adverse events:

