#### Adverse event (AE)

any untoward medical occurrence in a patient or clinical study subject. All such events, whether expected or not, will be recorded.

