#### Serious adverse event (SAE)

any untoward and unexpected medical occurrence or effect that: (1) results in death, (2) is life threatening (event in which the subject was at risk of death); (3) requires hospitalisation, or prolongation of existing inpatients’ hospitalisation; (4) results in persistent or significant disability or incapacity; (5) causes a congenital anomaly or birth defect. All SAEs will be collected and recorded whether they are ‘related’, that is, resulted from the administration of any of the research procedures, or ‘unexpected’, that is, an event that is not an expected occurrence. In the event of any SAE unblinding will occur to establish potential causality.

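### The stated 2–3 week safety review covers only the SHAPES and TENS arms, so minor early adverse events may be found more often there than in usual care

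*Protocol article*

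**What the plan says.** The Study procedures section, in its account of the second visit and what follows, sets out the mid-treatment contact. For everyone: "After 2–3 weeks all participants are contacted to check that they are managing the NRS-S diary". For SHAPES and TENS it adds: "with those in the device arms also receive a safety / device review with the study team". The same paragraph says that participants, and the clinicians who carry out the treatment checks, are not blinded to who is in the control group.

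Later contacts are not divided by arm. "At the end of the 6-week intervention period they return for end of treatment outcome measures", and "These assessments are repeated at 6 weeks, 12 weeks and 24 weeks after the end of intervention period".

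Under Safety reporting, the article says that "safety outcomes will also be reported". The adverse event definition covers any patient or study subject, and "All such events, whether expected or not, will be recorded". The serious adverse event rule begins "All SAEs will be collected and recorded whether they are" and is likewise not limited by arm. The Interventions section notes that "The participants in the usual care arm do not receive any device".

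The last paragraph of Outcome measures collects healthcare use at baseline, end of treatment (EOT) and each follow-up, by structured questionnaire and from electronic health records, with no restriction by arm.

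**The concern.** A rule that all events are recorded does not by itself make them equally likely to be found. Minor events often have to be asked about. The only safety enquiry that the article places within the treatment period goes to two arms of three, and blinding cannot offset this because device versus no device is open.

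Participants are 2–26 weeks after stroke, so background events are to be expected, and usual care is the only arm that shows their rate without stimulation. If that arm is asked less often, adverse event counts shift against both stimulation arms. For minor early events, part of any excess could then reflect the questioning rather than the treatment. The NRS-S efficacy analysis is not touched.

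**Working it through.** The article gives no adverse event rate or capture figure, so there is nothing to reproduce. The check has two parts.

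**1. The text.** One sentence describes the contact and says what each arm receives; the word joining the two halves marks the safety review as additional to the diary check. The asymmetry is therefore stated and does not have to be inferred from a missing detail. The all-arm recording rule sits beside it without an all-arm enquiry at that time point.

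**2. Possible size.** All inputs here are assumptions except the arm size, 297 / 3 = 99.

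- r: true risk of a minor adverse event over six weeks, equal in all arms.
- b: probability that an event is captured through contacts common to all arms.
- f: share of otherwise missed events that have already happened when the review takes place. With events and misses spread evenly over six weeks, f = 3/6 for a review at week 3 and 2/6 at week 2.
- s: probability that the review finds such an event. Setting s = 1 (a perfect review) gives a ceiling.

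Recorded risk is r × b in usual care and r × [b + f × s × (1 − b)] in a device arm. The ratio is 1 + f × s × (1 − b) / b, which does not depend on r.

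| b | Device capture, week 3, s = 1 | Ratio | Device capture, week 2, s = 1 | Ratio |
|---|---|---|---|---|
| 0.60 | 0.60 + 0.5 × 0.40 = 0.80 | 1.33 | 0.60 + 0.333 × 0.40 = 0.733 | 1.22 |
| 0.70 | 0.70 + 0.5 × 0.30 = 0.85 | 1.21 | 0.70 + 0.333 × 0.30 = 0.80 | 1.14 |
| 0.80 | 0.80 + 0.5 × 0.20 = 0.90 | 1.13 | 0.80 + 0.333 × 0.20 = 0.867 | 1.08 |
| 1.00 | 1.00 | 1.00 | 1.00 | 1.00 |

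A review that finds half of the reachable misses (s = 0.5, week 3, b = 0.70) gives 0.775 / 0.70 = 1.11.

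In absolute terms, with r = 0.30 and b = 0.70, recorded risks are 0.30 × 0.70 = 21% in usual care and at most 0.30 × 0.85 = 25.5% in a device arm. The gap is 4.5 points, or 99 × 0.045 = 4.5 participants per device arm.

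SHAPES versus TENS has ratio 1.00 throughout, because both arms get the same review. With the same enquiry in all arms, device versus usual care also has expected ratio 1.00 for any b, f and s.

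**The case against.** The strongest reply is that the article condenses a full protocol. It gives no schedule or script of adverse event enquiry for any arm, and naming the diary as the purpose of the usual care contact does not exclude a safety question there. This stands in part: it cannot be concluded that usual care is never asked. But the article does say what each arm receives at this contact, and the arms differ.

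Three further points stand and narrow the concern.

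- No between-arm test of harms is specified. The pairwise tests concern NRS-S success, and safety is only to be reported. A reader might infer that the harm comparison is biased as a matter of fact; the document supports only a risk of unequal capture in descriptive data. Counts shown by arm will still be compared.
- Sources common to all arms exist: the EOT and follow-up visits, and the healthcare-use questionnaire with record data. Hospital admissions and medically attended events should surface in every arm. What remains exposed is the minor, transient, unattended event of the first 2–3 weeks that is not recalled at week 6.
- Part of the review is a device check, which cannot apply to a participant without a device. Extra monitoring of those exposed is legitimate and is not the problem.

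A reader might also infer a larger effect, for example capture of 90% versus 70% (ratio 1.29) or 90% versus 60% (ratio 1.50). These require the review to recover 0.20 / 0.30 = two-thirds, or 0.30 / 0.40 = three-quarters, of all misses. Under even spread a review at week 3 can reach at most half. The larger figures need misses to be concentrated in the early weeks, which is possible but not shown.

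**Conclusion.** The point holds as a risk of differential ascertainment, limited to minor, transient, unattended adverse events from the first 2–3 weeks, and to device versus usual care. Its direction is against the device arms. Its size is unknown: at most about 1.1 to 1.3 on the ratio scale if common visits capture 60–80% of events, events and misses are spread evenly over six weeks and the review comes at week 3; smaller if the review comes sooner or is imperfect; and 1.00 if later visits capture everything. It could be larger if early events are the ones mainly forgotten. Serious and medically attended events are less exposed, and neither SHAPES versus TENS nor the efficacy analysis is affected. It merits a change because the remedy is nearly free, not because a bias has been demonstrated.

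**What to change.** At the existing 2–3 week contact, put the same scripted AE/SAE question to participants in all three arms and record the answers on the same form. Keep the device and skin check as a separate item for SHAPES and TENS. Report device-specific events separately from the three-arm adverse event summary. If the full protocol already asks usual care the same question, one sentence saying so settles the matter.

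The cost is one question in a contact that already reaches every usual care participant, with no extra visit or staff, and a few more forms in that arm. Participants already past the contact stay unequal and must be flagged. There may be many of them: recruitment was planned to end in December 2024, the month after the article appeared. For these participants, the report should state the difference in enquiry beside the device versus usual care counts.
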